### 2.6. Nonadherence Criteria and Extension of the Intervention

Patients will be considered adherent to the RIPC protocol if they complete a minimum of 70% of the planned sessions within the specified period. Compliance with the intervention will be monitored and documented periodically throughout this study via weekly phone calls and biweekly visits. Should a participant need to pause RIPC due to unforeseen reasons during the three-month intervention, the duration may be extended by up to four additional weeks.

### 2.7. Outcomes

All outcomes will be collected and assessed by registered nurses who are members of the research team; however, they will not be blinded, as they will also be responsible for monitoring compliance and instructing patients on the application of the RIPC.

#### 2.7.1. Primary Outcomes

Exercise capacity:-Six-Minute Walking Test (6MWT): This test will be conducted in a 30 m long corridor. The participants will walk back and forth along this section, which will be marked with cone-shaped markers placed 29 m apart, leaving 0.5 m at each end to facilitate turns. The test will be supervised by the examiner.

Endothelial function:-Carotid Intima-Media Thickness (CIMT): CIMT will be assessed via ultrasound using the Sonosite SII device, Bothell, WA, USA. CIMT is an independent predictor of future clinical events such as myocardial infarction and sudden cardiac death [40] and allows for the assessment of structural changes over time, facilitating the monitoring of atherosclerosis [41].

Arterial stiffness:-Pulse wave velocity (PWV), the radial augmentation index (rAIx), and the central augmentation index (cAIx): These measurements will be obtained via the SphygmoCor System (AtCor Medical Pty Ltd., West Ryde, NSW, Australia) while the patient is lying in a supine position. Pulse waves will be recorded from the carotid and femoral arteries. The rAIx is calculated as follows: (Second systolic peak [SBP2] − Diastolic blood pressure [DBP]) divided by (First systolic peak − DBP), multiplied by 100 (%). The cAIx is calculated as follows: central pulse pressure augmentation times 100 divided by pulse pressure. All indices will be derived directly from the respective devices.

#### 2.7.2. Covariates

Sociodemographic variables and medical history were collected via self-reports.

Sociodemographic Variables

-Age.-Sex.-Socioeconomic status: Participants reported their socioeconomic and employment status. These factors will be used to calculate an index based on the Spanish Society of Epidemiology scale.

Medical history

-Comorbidities: Chronic conditions such as hypertension, diabetes, COPD, smoking, and alcohol use will be recorded.-Pharmacological treatment: Pharmacological therapies followed by each patient will be collected through questionnaires.

Anthropometric Variables

-Weight: Weight will be recorded as the mean of two measurements using a Seca^®^ 861 scale, with participants barefoot and in light clothing.-Height: The average of two measurements will be taken using a wall-mounted stadiometer (Seca^®^ 222, Hamburg, Germany), with participants standing barefoot, upright, and with their sagittal midline aligned to the stadiometer.-Body mass index (BMI): BMI will be calculated via the following formula: weight (kg) divided by height squared (m^2^).-Waist circumference: The average of three measurements will be recorded via a flexible tape measure at the midpoint between the lowest rib and the iliac crest, taken at the end of a normal exhalation.-Body fat percentage: The mean of two assessments will be obtained via the Tanita^®^ BC-418 MA eight-electrode bioelectrical impedance (Tanita Corp., Tokyo, Japan).-Blood pressure: We will record the mean of two readings taken 5 min apart using an Omron^®^ HEM-907 monitor (Omron Healthcare Milton Keynes, UK Ltd.), after a 5 min rest, with the patient seated in a quiet environment and the right arm semiflexed at heart level. Cuffs of three sizes will be used depending on the arm circumference.

Muscle strength:-Handgrip strength will be measured using a TKK 5401 grip-D dynamometer (Takei^®^, Tokyo, Japan). Two measurements will be taken on each arm, and the average will be calculated. The hand size will be taken into consideration to adjust the dynamometer grip accordingly.

Step Cadence, Heart Rate, Sleep Quality and Duration, and METs (Metabolic Equivalents):-Variables such as step cadence (steps/min), METs (activity-related energy expenditure), and heart rate (beats/min) will be continuously recorded at 1 min intervals via the Fitbit Inspire 3 activity tracker, which will be worn for 9 days.-Aggregated metrics of sleep quality and duration will be recorded daily on the basis of Fitbit data, providing a comprehensive assessment of participants’ sleep patterns.

Biochemical parameters

Blood samples will be collected from an antecubital vein between 8:15 and 9:00 a.m. after a minimum 12 h fast. Three aliquots will be frozen: one for the purposes of the current study and two for potential future analyses (with the participants’ informed consent).

-The following biomarkers will be evaluated: glucose, total cholesterol, triglycerides, HDL and LDL cholesterol, apolipoproteins A1 and B, insulin, and high-sensitivity C-reactive protein (hsCRP). These analyses will be conducted via the Cobas 8000 system (Roche Diagnostics^®^), while insulin levels will be measured on the Architect platform (Abbott^®^).-HbA1c Glycated haemoglobin will be analysed via high-performance liquid chromatography (HPLC) via the ADAMS A1c HA-8180 V analyser (A. Menarini Diagnostics^®^), which is certified by both the NGSP and the IFCC.

Genotyping:-Genotyping will be performed using a saliva sample collected in a sterile tube mixed with a preservative reagent. A sufficient volume (1–3 mL) is required to ensure adequate DNA content for analysis.

Physical Activity:-International Physical Activity Questionnaire (IPAQ): The IPAQ assesses physical activity by classifying it into three intensity levels and calculates weekly energy expenditure in MET minutes.

Physical Fitness:-International Fitness Scale (IFIS): A validated self-report assessment questionnaire was used to assess perceived physical fitness.

Diet:-Mediterranean Diet Adherence Screener (MEDAS-14): A 14-item validated questionnaire will be used to evaluate adherence to the Mediterranean dietary pattern.-Processed Food Consumption Questionnaire (SQ-HPF): A validated questionnaire evaluating the frequency and quantity of intake in 14 food categories will be used.

Quality of Life:-Short Form Health Survey (SF-12);-Minnesota Living with Heart Failure Questionnaire (MLWHFQ).

### 2.8. Ethical Considerations

The study protocol received approval from the Clinical Research Ethics Committee of the Hospital Virgen de la Luz in Cuenca, the site where the research will be carried out (REG: 2025/PI0625).

In compliance with Spanish Law 3/2018 of 5 December on the Protection of Personal Data and Guarantee of Digital Rights (LOPD-GDD), the rights and freedoms of study subjects will be respected, including the confidentiality of their data.

Participants will be informed at every stage of this study regarding its objectives and methodology and will be asked to provide written informed consent.

### 2.9. Sample Size Calculation

The sample size was calculated using Epidat 4.2 software, which is based on the data reported by Maxwell et al. [42]. To achieve 90% statistical power and a significance level of 0.05, a sample size of 20 patients per group is needed to detect a statistically significant difference in flow-mediated dilatation. Assuming a 20% dropout rate, the final sample size is estimated at 48 participants (24 in each group).

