### 2.4. Randomisation

Participants will be randomly assigned (1:1) via EPIDAT version 4.2 software (Figure 1) to one of two groups: Group 1, RIPC; Group 2, the control group (CG). Prior to randomisation, screening will be performed, and all participants will be required to sign the informed consent form.

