### 2.11. Mitigation Strategies

Heterogeneity among participants.
○To reduce heterogeneity among participants, the established inclusion and exclusion criteria will be rigorously applied, thereby ensuring a more homogeneous sample.

Dropouts and missing data
○Qualified nursing staff from the research team will be responsible for training participants in the correct application of the therapy, as well as monitoring follow-up diaries and providing reminders via weekly phone calls and biweekly visits to ensure adequate compliance and minimise losses during follow-up. In addition, analyses will be conducted according to the intention-to-treat principle, meaning that all participants will be included in the primary analysis, regardless of whether or not they complete the intervention. With respect to the treatment of missing data, appropriate statistical methods, such as imputation techniques, can be applied to reduce the bias associated with missing information.

Small sample size.
○Although the sample size is small, it has been calculated on the basis of previous estimates and a dropout rate of 20%, which has been incorporated into the calculation to ensure the minimal statistical power required to detect relevant effects.

Exercise tolerance may be influenced by participants’ daily activities.
○Participants will be instructed to maintain their usual lifestyle during their involvement in this study. To monitor this, measurements will be taken via activity trackers, the 6MWT, and self-reported physical activity questionnaires.

Lack of blinding.
○The absence of blinding in both participants and research staff could influence the subjectivity of some assessments. To mitigate this limitation, objective measures, such as anthropometric parameters, blood pressure, biochemical markers, muscle strength tests, and exercise capacity assessments, among others, will be included. Similarly, to reduce bias resulting from the lack of blinding in the research team, standardised protocols for data collection will be applied.

Potential bias.
○To mitigate potential bias, confounding variables such as medication, age, sex, and socioeconomic status will be considered in the analyses.

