### 4.4. RIPC, HFpEF, and Arterial Stiffness

Arterial stiffness, particularly of the aorta, increases the load on the left ventricle, adversely affecting its structure and function. These changes contribute to the development of diastolic dysfunction, which is a key factor in HFpEF. Moreover, increased carotid–femoral pulse wave velocity has been associated with a greater risk of heart failure [47]. Given the contribution of arterial stiffness to HFpEF, interventions that target this parameter may prove beneficial in its management. To date, RIPC has shown inconclusive results in patients with peripheral arterial disease [48] and angina pectoris [42]; however, its effects have not yet been demonstrated in individuals with HFpEF.

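### The sample size and 90% power are stated for flow-mediated dilatation, which is not a listed outcome, so the power claim is unsupported for all five listed primary outcomes

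*Protocol article*

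**What the plan says.** Section 2.9 sets its targets ("To achieve 90% statistical power and a significance level of 0.05") and concludes that "a sample size of 20 patients per group is needed to detect a statistically significant difference in flow-mediated dilatation". The calculation is one "which is based on the data reported by" an earlier trial, reference 42, which section 4.4 places in angina pectoris. No difference, SD or sidedness is stated. A 20% dropout allowance takes the total to 48, or 24 per group.

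Section 2.7.1 lists five primary measures in three domains:

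- exercise capacity: 6MWT
- endothelial function: one measure only, "Carotid Intima-Media Thickness (CIMT): CIMT will be assessed via ultrasound using the Sonosite SII device"
- arterial stiffness: PWV, rAIx and cAIx

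FMD is not in this list, nor in the covariates (2.7.2), the statistical analysis (2.10) or the discussion. Section 2.9 is the only place in the text where it occurs.

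Section 2.11 answers the worry about a small sample by pointing back to this calculation, which is said "to ensure the minimal statistical power required to detect relevant effects".

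**The concern.** A power figure belongs to one endpoint, one assumed difference and one SD. Here it belongs to an endpoint that the article does not list, while the endpoints it does list have no power statement at all. CIMT, the one listed measure of endothelial function, cannot inherit the figure. It is a different quantity, and section 2.7.1 itself presents it as a measure of structural change.

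Readers and ethics reviewers use section 2.9 to judge whether 48 patients can answer the trial's questions. As written, they would take the trial to have 90% power for its primary outcomes. They could later read a non-significant result on 6MWT, PWV or CIMT as coming from a trial with that power. Nothing in the article corrects this impression: section 4.6 mentions a loss of power only if recruitment falls short.

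**Working it through.** **Inputs from the article.** 20 evaluable per group, power 90%, alpha 0.05, dropout 20% and total 48 (section 2.9); 1:1 allocation (2.4); ANCOVA adjusted for baseline (2.10).

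**Inputs not in the article, taken as assumptions.** Two-sided test; baseline-to-follow-up correlation r from 0.5 to 0.9; true standardised differences d (difference divided by SD) from 0.3 to 1.0.

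**1. The plan's own figure.** The 20 per group cannot be recomputed forwards, since no difference or SD is given. The step from 20 to 24 can: 20 × 1.20 = 24 per group, 48 in total. (Dividing by 0.80 gives 25 per group, 50 in total. That two-patient gap is not part of this point.)

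**2. Back-solving for the implied effect.** Normal approximation:

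d = (z for 0.975 + z for 0.90) × √(2/n) = (1.960 + 1.282) × √(2/20) = 3.242 × 0.3162 = 1.03.

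With the noncentral t distribution (38 degrees of freedom), d = 1.05. A one-sided test would give 0.93 and 0.94 respectively. These describe the effect that 20 per group can detect. They describe FMD only insofar as FMD was the endpoint used.

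**3. Under the planned ANCOVA.** Baseline adjustment multiplies the residual SD by √(1 − r²), so the difference detectable with 90% power is 1.052 × √(1 − r²):

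| Assumed r | √(1 − r²) | Detectable d |
|---|---|---|
| 0.5 | 0.866 | 0.91 |
| 0.7 | 0.714 | 0.75 |
| 0.8 | 0.600 | 0.63 |
| 0.9 | 0.436 | 0.46 |

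This ignores the degrees of freedom spent on the other covariates, so it is slightly favourable on that count.

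**4. Power at 20 per group for assumed true effects.** Power is from the unadjusted two-sided t-test; n is from the normal approximation, before dropout.

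| Assumed d | Power, 20 per group | n per group for 90% |
|---|---|---|
| 0.3 | 15% | 234 |
| 0.5 | 34% | 85 |
| 0.8 | 69% | 33 |
| 1.0 | 87% | 22 |

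For d = 0.5 with ANCOVA at r = 0.7, the effective difference is 0.5 / 0.714 = 0.70 and power is 58%.

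**5. What follows.** Power for the listed outcomes could be anywhere in this range or above it, depending on quantities the article does not give. The 90% cannot be attached to any of them on what is written.

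**The case against.** Four objections deserve weight.

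- **FMD may be measured but unlisted.** A reader might infer that the trial does not measure FMD. The article does not establish that. It is condensed, and its outcome list is visibly incomplete: diastolic function is a stated objective in the abstract, introduction and discussion, yet section 2.7 gives no measure for it. Endothelial function is a primary domain, so FMD may have been left out of the list and not out of the study. This objection stands, and the fix must allow for both cases.
- **Low power is not demonstrated.** A reader might infer that the trial is underpowered for its primary outcomes. That is not shown either. The effects and correlations in the working are assumptions, and 90% power is reached at 0.46 SD if r is 0.9. This stands: the defect is an unsupported claim, not a proven shortfall.
- **The source and the missing inputs are not errors in themselves.** Section 1 says that no RIPC trial has been done in HFpEF, so an estimate from another population is understandable. An article may leave the effect size and SD to the full protocol. The inconclusive results reported in section 4.4 concern arterial stiffness and do not bear on an FMD calculation. All of this stands, and the point does not rest on any of it.
- **Confidence intervals will be reported.** Section 2.10 promises 95% intervals, which govern what a null result excludes far better than planned power does. This limits the consequence but leaves the power statement in 2.9 uncorrected.

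None of these removes the mismatch. Condensing does not explain it well: the article details its measures down to corridor markings and scale models, and it positively states a power figure for an endpoint that is not among them.

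**Conclusion.** Sections 2.9 and 2.7.1 are inconsistent and must be reconciled. The 90% power statement, and section 2.11's reliance on it, is unsupported for all five listed primary outcomes. At 20 evaluable patients per group and two-sided 5%, those outcomes would have 90% power only if the true standardised difference were about 1.05 unadjusted, or about 0.91 to 0.46 under ANCOVA. These figures rest on an assumed two-sided test and an assumed baseline correlation of 0.5 to 0.9. Whether such effects are plausible for 6MWT, CIMT, PWV, rAIx or cAIx in HFpEF cannot be judged from the article. The correction is needed because this is the trial's only sample size justification and the article relies on it elsewhere.

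**What to change.** Keep 48 patients and amend the text according to the facts:

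- **If FMD is measured:** list it in section 2.7.1 as the outcome that sizes the trial, and state in 2.9 that the 90% power applies to FMD only.
- **If FMD is not measured:** remove the FMD power claim. Restate section 2.9 as the difference detectable with 20 evaluable patients per group for one named, measured primary outcome under the planned ANCOVA. State the SD, the baseline correlation and the sidedness as assumptions.
- **In either case:** say in 2.9 and 2.11 that the remaining primary outcomes are not formally powered.

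The cost is rewording two or three sections and, in the second case, finding a defensible SD and correlation, which the article does not supply. No patients are added, and no procedures beyond those already planned. The downside is a less favourable power statement.

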## Abstract

**Background/Objectives**: Heart failure with preserved ejection fraction (HFpEF) has increased in prevalence as the population ages and associated comorbidities increase. Remote ischemic preconditioning (RIPC) has been shown to provide protection against ischemic injury to the heart and other organs. Therefore, the aim of this project will be to analyse the effectiveness of RIPC in terms of arterial stiffness, endothelial function, diastolic function, and exercise capacity in patients with HFpEF. **Methods**: The PIRIC-FEp study will be a parallel, randomised controlled trial with two groups conducted at the Faculty of Nursing in Cuenca, University of Castilla-La Mancha. Individuals who are diagnosed with HFpEF and are older than 40 years, with a left ventricular ejection fraction ≥50% and a sedentary lifestyle, will be included. The exclusion criteria will include, among others, patients with noncardiac causes of heart failure symptoms, significant pulmonary disease, diabetes, peripheral vascular disease, or myocardial infarction within the previous three months. A sample size of 48 patients was estimated, with 24 for each group. Participants will be randomly allocated (1:1) to either the RIPC intervention group or the control group to evaluate the effects on arterial stiffness, endothelial function, diastolic function, and exercise capacity. Assessments will be conducted at baseline and after a three-month follow-up period. **Results**: The findings will be published in a peer-reviewed journal article. **Conclusions**: This study is important for daily clinical practice because it provides a new approach for the treatment of HFpEF patients via RIPC.

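### The 20% dropout allowance in section 2.9 is computed as 20 × 1.2 = 24 per group instead of 20 / 0.8 = 25, so 24 per group falls just short of the 20 evaluable patients required

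*Protocol article*

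**What the plan says.** Section 2.9 of the protocol article (Sample Size Calculation) sets the target "To achieve 90% statistical power and a significance level of 0.05" and concludes that "a sample size of 20 patients per group is needed to detect a statistically significant difference in flow-mediated dilatation". It then adds the allowance for losses: "Assuming a 20% dropout rate, the final sample size is estimated at 48 participants (24 in each group"). Allocation is 1:1 (section 2.4).

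The abstract repeats the total: "A sample size of 48 patients was estimated, with 24 for each group". Section 2.11 (Mitigation Strategies) answers the worry about a small sample by pointing to "a dropout rate of 20%, which has been incorporated into the calculation", with the stated aim of securing the minimum power needed.

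Section 2.9 takes its inputs from a cited study. It prints no effect size, no standard deviation and no sidedness of the test.

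**The concern.** The three figures in section 2.9 (20 needed, 20% lost, 24 randomised) cannot all hold. A dropout rate is the share of randomised patients who are lost, so the required number has to be divided by the share retained. Adding 20% of the required number gives too few.

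What is at stake is the stated safeguard. Section 2.11 offers the dropout allowance as the reason why a small trial still keeps its power, and section 4.6 already concedes that recruitment may fall short of target. The plan should therefore say correctly how much loss the 48 patients can absorb.

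**Working it through.** **Inputs**

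- Evaluable patients needed per group: 20 (section 2.9).
- Dropout rate: 20% (sections 2.9 and 2.11).
- Randomised: 24 per group, 48 in total (section 2.9, abstract).
- Power 90%, significance level 0.05 (section 2.9). Two-sided is my assumption.

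**Step 1: reproduce the plan's figure.** Required number × (1 + dropout) = 20 × 1.2 = 24 per group, and 2 × 24 = 48. This matches exactly.

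**Step 2: apply the rate to those randomised.** Required number / (1 − dropout) = 20 / 0.8 = 25 per group, and 2 × 25 = 50. The result is a whole number, so rounding cannot turn it into 24.

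**Step 3: see what 24 delivers.**

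- Expected to remain at 20% dropout: 24 × 0.8 = 19.2 per group, or 38.4 in total against 40 required.
- In whole patients, losing 4 of 24 leaves 20 and losing 5 leaves 19.
- Largest dropout that still leaves 20: 1 − 20/24 = 4/24 = 16.7%.
- Shortfall in the number randomised: 25 − 24 = 1 per group, 50 − 48 = 2 in total.

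**Step 4: what this means for power.** With no effect size or SD in the document, I solved for the standardised difference that gives 90% power at the unrounded sample size, then computed power at the reduced numbers. The comparison is an unadjusted two-sided two-sample t test (noncentral t). Because a sample size is normally rounded up, the unrounded requirement may lie anywhere from just above 19 to 20, so I took both ends.

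| Assumption about the 20 | Standardised difference | Power at 20 | Power at 19.2 | Power at 19 |
|---|---|---|---|---|
| 20 gives exactly 90% | 1.052 | 90.0% | 88.7% | 88.4% |
| Rounded up from 19.01 | 1.081 | 91.5% | 90.3% | 90.0% |

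Under the first assumption, a normal approximation gives nearly the same answer: 88.8% at 19.2 and 88.5% at 19. At 20% dropout the range is therefore about 88.4% to 90.3%.

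**The case against.** The strongest reply is that this changes almost nothing. Two more patients would alter neither the design nor the analysis, and at most about 1.6 percentage points of power are involved (90.0% − 88.4%). That stands, and it sets the weight of the point.

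A reader might go further and infer that the trial loses its 90% power. The documents do not support that. If the 20 was rounded up from just above 19, power at 20% dropout is still about 90%, and without the inputs to the calculation nobody can tell which end applies. The power figures also describe an unadjusted comparison of flow-mediated dilatation. The planned analysis is an ANCOVA adjusted for baseline and other covariates (section 2.10), and flow-mediated dilatation is not among the primary outcomes listed in section 2.7.1. The range therefore says little about the power of the analyses that will be reported.

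A reader might also infer that the sections disagree with one another. They do not: the abstract and section 2.9 give the same total, and section 2.11 gives only the rate. The fault lies in the step from 20 to 24.

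Finally, one could say that intention-to-treat analysis, possible imputation, weekly calls and biweekly visits cover the gap. The calls and visits may lower dropout, but the calculation assumes 20%. Imputation is optional in section 2.11, is offered there to reduce bias, and does not in general restore the information that is lost. This part of the reply does not repair the figure.

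**Conclusion.** The point holds as a small arithmetic error. On the protocol's own numbers, 24 per group leaves 19.2 at 20% dropout, below the 20 said to be needed; it covers losses only up to 16.7%. That conclusion needs no assumption beyond reading dropout as a share of those randomised. The size is 1 patient per group, 2 in total.

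The consequence for power is less certain: about 88.4% to 90.3% at 20% dropout, conditional on a two-sided unadjusted comparison and on how the 20 was rounded. This does not show a materially underpowered trial. It shows that the assurance in section 2.11 is not met, as worded, by the sample size in section 2.9.

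**What to change.** Preferred, with no extra recruitment: keep 48. In section 2.9, state that 24 per group retains 20 evaluable patients for dropout up to 16.7%, and about 19 per group at 20%. If a power figure at 20% dropout is added, derive it from the actual Epidat inputs and print those inputs with it; otherwise give it only as a conditional range. In section 2.11, change the statement that 20% dropout has been built in so that it matches. The abstract needs no change. The cost is one or two sentences.

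Alternative, if full cover for 20% dropout is wanted: change the sample size to 25 per group, 50 in total, in section 2.9 and the abstract. Section 2.11 can then stand. The cost is two more patients and the usual amendment.
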